###### **3.13.6. Day 1, 2**

On days 1 and 2, CPT sessions 1-4 and the 45-minute preparatory session (on day 2) will be completed. Also, PTSD Checklist-5 (PCL-5), Patient Health Questionnaire-9 (PHQ-9), Working Alliance Inventory-Short Form (WAI-SF), World Health Organization Well-Being Index, 5-item (WHO-5), Generalized Anxiety Disorder Scale, 7-item (GAD-7), Columbia Suicide Severity Rating Scale (C-SSRS) since last visit, AEs and concomitant medications review will be administered virtually by the study coordinator.

###### **3.13.7. Day 3 (Dosing Day)**

25 mg psilocybin will be administered on day 3 (6-8 hours). The following scales will be collected in person:

| **Pre-dose assessments** | **Post-dose assessments** |
| --- | --- |
| - **AEs** - **Concomitant medications** - **Vital signs** - **Contraceptive method review** - **Pregnancy screening through a personal urine test** - **Columbia Suicide Severity Rating Scale (C-SSRS) since last visit** - **Posttraumatic Stress Disorder Checklist for the DSM-5 (PCL-5)** - **Patient Health Questionnaire-9 (PHQ-9)** - **Working Alliance Inventory- Short Form (WAI-SF)** - **World Health Organization Well-Being Index, 5-item (WHO-5)** - **Generalized Anxiety Disorder Scale, 7-item (GAD-7)** | - **Columbia Suicide Severity Rating Scale (C-SSRS) since last visit** - **AEs** - **Vital signs** - **Working Alliance Inventory- Short Form (WAI-SF)** - **Psychological Insight Questionnaire (PIQ)** - **Emotional Breakthrough Inventory (EBI)** - **Altered States of Consciousness Rating Scale (ASC)** - **Acceptance/Avoidance-Promoting Experiences Questionnaire (APEQ)** |

Post dose assessments will be completed after the acute effects of psilocybin are resolved. Upon completion of the post-dose assessments, the participant will be assessed for safe discharge under the supervision of a designated chaperone.

###### **3.13.8. Day 4-7**

The 1-hour integration session and CPT sessions 5 and 6 will be completed virtually on the day after the dosing session (day 4). Moreover, CPT sessions 7–12 will be completed virtually twice from day 5 to day 7. The follow-up assessments are specified in the Schedule of Assessments (Table 2).

###### **3.13.9. Follow-up Assessments**

The follow-up assessments as specified in the Schedule of Assessments (Table 2) will be conducted weekly from week 2 until week 13. Week 2 to week 12 follow-up assessments will be conducted virtually, and week 13 will be conducted in person. A narrative, qualitative survey at weeks 5 and 13 will evaluate participant experiences with psilocybin-assisted CPT and the wearable device. Participants will return Oura to study coordinator or research assistant at week 13. The interviews will be conducted by the study coordinator or research assistant and take approximately 45-60 minutes to complete. We will also use User Experience Questionnaire.

Qualitative survey questions will include:

1. Think back to yourself before you heard about the study—Can you briefly describe what your experience of posttraumatic stress disorder was like?

2. What happened during the session when you were given the psilocybin? Please describe your experience.

3. What were cognitive processing therapy sessions like for you? Please describe your experience.

4. Has the treatment had any effect, positive or negative, on your posttraumatic stress disorder and life? Have you noticed any changes in yourself, your thinking, your emotions, or your behaviors?

5. What do you attribute those changes to? How do you think the psilocybin experience contributed to these changes? How do you feel the cognitive processing therapy sessions contributed to these changes?

6. Is there anything that you would change about the intervention? What was it like for you to do an intensive one week treatment?

7. Anything else you would like to add about your experience with the treatment or about its effects on your posttraumatic stress disorder?

8. You have also been using the Oura Ring over the past ______ weeks. What was your experience like with this platform? Were there any specific barriers to use that you found? Did you find this platform helped you in understanding your mental state and well-being over the past few weeks?

**Table 3. User Experience Questionnaire.**

|  | 1 | 2 | 3 | 4 | 5 | 6 | 7 |  |
| --- | --- | --- | --- | --- | --- | --- | --- | --- |
| annoying | ⚪ | ⚪ | ⚪ | ⚪ | ⚪ | ⚪ | ⚪ | enjoyable |
| not understandable | ⚪ | ⚪ | ⚪ | ⚪ | ⚪ | ⚪ | ⚪ | understandable |
| creative | ⚪ | ⚪ | ⚪ | ⚪ | ⚪ | ⚪ | ⚪ | dull |
| easy to learn | ⚪ | ⚪ | ⚪ | ⚪ | ⚪ | ⚪ | ⚪ | difficult to learn |
| valuable | ⚪ | ⚪ | ⚪ | ⚪ | ⚪ | ⚪ | ⚪ | inferior |
| boring | ⚪ | ⚪ | ⚪ | ⚪ | ⚪ | ⚪ | ⚪ | exciting |
| not interesting | ⚪ | ⚪ | ⚪ | ⚪ | ⚪ | ⚪ | ⚪ | interesting |
| unpredictable | ⚪ | ⚪ | ⚪ | ⚪ | ⚪ | ⚪ | ⚪ | predictable |
| fast | ⚪ | ⚪ | ⚪ | ⚪ | ⚪ | ⚪ | ⚪ | slow |
| inventive | ⚪ | ⚪ | ⚪ | ⚪ | ⚪ | ⚪ | ⚪ | conventional |
| obstructive | ⚪ | ⚪ | ⚪ | ⚪ | ⚪ | ⚪ | ⚪ | supportive |
| good | ⚪ | ⚪ | ⚪ | ⚪ | ⚪ | ⚪ | ⚪ | bad |
| complicated | ⚪ | ⚪ | ⚪ | ⚪ | ⚪ | ⚪ | ⚪ | easy |
| unlikable | ⚪ | ⚪ | ⚪ | ⚪ | ⚪ | ⚪ | ⚪ | pleasing |
| usual | ⚪ | ⚪ | ⚪ | ⚪ | ⚪ | ⚪ | ⚪ | leading edge |
| unpleasant | ⚪ | ⚪ | ⚪ | ⚪ | ⚪ | ⚪ | ⚪ | pleasant |
| secure | ⚪ | ⚪ | ⚪ | ⚪ | ⚪ | ⚪ | ⚪ | not secure |
| motivating | ⚪ | ⚪ | ⚪ | ⚪ | ⚪ | ⚪ | ⚪ | demotivating |
| meets expectations | ⚪ | ⚪ | ⚪ | ⚪ | ⚪ | ⚪ | ⚪ | does not meet expectations |
| inefficient | ⚪ | ⚪ | ⚪ | ⚪ | ⚪ | ⚪ | ⚪ | efficient |
| clear | ⚪ | ⚪ | ⚪ | ⚪ | ⚪ | ⚪ | ⚪ | confusing |
| impractical | ⚪ | ⚪ | ⚪ | ⚪ | ⚪ | ⚪ | ⚪ | practical |
| organized | ⚪ | ⚪ | ⚪ | ⚪ | ⚪ | ⚪ | ⚪ | cluttered |
| attractive | ⚪ | ⚪ | ⚪ | ⚪ | ⚪ | ⚪ | ⚪ | unattractive |
| friendly | ⚪ | ⚪ | ⚪ | ⚪ | ⚪ | ⚪ | ⚪ | unfriendly |
| conservative | ⚪ | ⚪ | ⚪ | ⚪ | ⚪ | ⚪ | ⚪ | innovative |

###### **4. Safety**

The safety of participants will be assured before, during and after the psilocybin dosing session and during the study period by assessing physiological effects, psychological distress, medical events, AEs, TEAEs, SAEs, AESIs, spontaneously reported reactions, concomitant medication use, and suicidal ideation and behavior.

- Suicidality will be assessed with the Columbia Suicide Severity Rating Scale (C-SSRS) throughout the study.
- Vital signs including blood pressure, heart rate and temperature will be measured before and after the dosing session.
- SAEs, TEAEs and SAEs will be collected. All medical events and spontaneously reported reactions will be collected throughout the study.
- Events requiring medical attention will be collected through termination.
- Any event leading to withdrawal from the protocol will be collected throughout the study.
- All events related to changes in psychiatric status will be collected throughout the study.
- Baseline medications and changes to psychiatric medications will be collected throughout the study.

###### **4.1. Adverse Events**

An AE is the development of an undesirable medical condition or the deterioration of a pre-existing medical condition following or during exposure to a pharmaceutical product, whether or not considered causally related to the product. An undesirable medical condition can be symptoms (e.g., nausea, chest pain), signs (e.g., tachycardia, enlarged liver) or the abnormal results of an investigation (e.g., laboratory findings, electrocardiogram). In clinical studies, an AE can include an undesirable medical condition occurring at any time, including run-in or washout periods, even if no study treatment has been administered.

###### **4.1.1. Assessment of Intensity**

Each AE will be classified according to the following criteria:

- Mild: The AE does not interfere in a significant manner with the participant’s normal level of functioning.
- Moderate: The AE produces some impairment of functioning, but is not hazardous to the participant’s health.
- Severe: The AE produces significant impairment of functioning or incapacitation and is a definite hazard to the participant’s health.

When changes in the intensity of an AE occur more frequently than once a day, the maximum intensity for the experience should be noted. If the intensity category changes over several days, those changes should be recorded separately (with distinct onset dates).

###### **4.1.2. Assessment of Causality**

All AEs will be assessed by a blinded study investigator as to whether they can be explained by the participant’s underlying condition. If they are not explainable, then the study investigator will make a determination of the relationship of the AE with psilocybin as follows:

- **Probable:** Reports including good reasons and sufficient documentation to assume a causal relationship, in the sense of plausible, conceivable, likely, but not necessarily highly probable. A reaction that follows a reasonable temporal sequence from administration of psilocybin; that follows a known or expected response pattern to the suspected medicine; or that is confirmed by stopping or reducing the dosage of the medicine and that could not reasonably be explained by known characteristics of the participant’s clinical state.
- **Possible:** Reports containing sufficient information to accept the possibility of a causal relationship, in the sense of not impossible and not unlikely, although the connection is uncertain or doubtful, for example because of missing data or insufficient evidence. A reaction that follows a reasonable temporal sequence from administration of the psilocybin; that follows a known or expected response pattern to the suspected medicine; but that could readily have been produced by a number of other factors.
- **Unlikely:** Reports not following a reasonable temporal sequence from psilocybin administration. An event which may have been produced by the participant’s clinical state or by environmental factors or other therapies administered.
- **Not related (unrelated):** Events for which sufficient information exists to conclude that the etiology is unrelated to the psilocybin.
- **Unclassified:** Reports which for one reason or another are not yet accessible (e.g., because of outstanding information (can only be a temporary assessment)).

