# **Study Summary**

| Name of Sponsor-Investigator:  [name], St. Michael’s Hospital | |
| --- | --- |
| Name of Investigational Product:  Psilocybin | Protocol Identification Code:  23-230 |

**ClinicalTrials.gov Number**: Not yet assigned

**Clinical Phase**: 2

| Title | Psilocybin-Assisted Massed Cognitive Processing Therapy for Chronic Posttraumatic Stress Disorder: An Open-label Trial |
| --- | --- |
| Sources of monetary or material support | Internal sources of funding |
| Brief title | Psilocybin-assisted CPT for PTSD |
| Indication: | Adults with Chronic Posttraumatic Stress Disorder (PTSD) |
| Condition(s) or focus of study | Posttraumatic Stress Disorder |
| Number of participants | 15 |
| Primary outcome | To determine the feasibility and tolerability of psilocybin-assisted cognitive processing therapy (CPT) in adults with chronic PTSD (i.e., recruitment rate, withdrawals, data completion, adherence, and number and nature of adverse events). |
| Secondary outcomes | 1. To examine the effect of psilocybin-assisted CPT on clinician-rated PTSD symptoms, self-reported treatment outcomes (e.g., depression and anxiety severity, psychological functioning, sleep quality) and putative mechanisms of change. |
| Exploratory outcomes | 1. To evaluate the effect of psilocybin-assisted CPT on digital physiological passive data collected through the use of a wearable device (Oura Ring). 2. To create a personal digital phenotype profile (pDPP) based on the wearable’s and clinical assessments’ data. |
| Safety outcome | 1. To evaluate the safety of psilocybin-assisted CPT in adults with chronic PTSD. |
| Study design | Study type: Open-label  Allocation: N/A  Intervention model: Single arm  Primary outcome: Feasibility  Phase: 2 |
| Masking | N/A |
| Date of enrollment | Start date: Upon REB Approval  End date: Dependent on REB Approval |

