###### **4.1.6. Recording of Adverse Events**

AEs will be collected from day 1 of treatment week until the end of the study. At each visit, subjects will be asked if they have had any health problems since the previous visit. All AEs will be recorded appropriately, whether or not considered related to the investigational product. This will include AEs spontaneously reported by the patient and/or observed by the staff as well as AEs reported in response to a direct question e.g. “Have you had any health problems since your last visit?”

For each AE, the following parameters will be described: discovery (i.e., spontaneous or solicited); start; end date or ongoing; action taken with regards to investigational product; outcome if the AE caused the patient to discontinue; a statement if the AE fulfills the criteria for a SAE or not; the investigator’s assessment of the causal relationship between the event and the investigational product; intensity of the AE, i.e., mild (awareness of sign or symptom, but easily tolerated), moderate (discomfort sufficient to cause interference with normal activities), severe (incapacitating, with inability to perform normal activities); and resolution.

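### Section 4.1.2 gives AE assessment to a blinded investigator in an open-label single-arm trial and rates the relationship to psilocybin only for AEs the underlying condition cannot explain, contradicting section 4.1.6 and its own causality scale

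*Protocol*

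**What the plan says.** Section 4.1.2 sets out two steps. First: "All AEs will be assessed by a blinded study investigator", the question being whether the underlying condition can explain the event. Then: "If they are not explainable, then the study investigator will make a determination of the relationship of the AE with psilocybin", on a scale from *Probable* to *Not related*, with *Unclassified* as a temporary category.

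Section 4.1.6, on recording, is broader. It opens its list with "For each AE, the following parameters will be described", and one of the items is "the investigator’s assessment of the causal relationship between the event and the investigational product". It mentions neither blinding nor a preliminary question about the underlying condition.

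On design, the Study Summary gives "Study type: Open-label" and "Intervention model: Single arm", with allocation and masking both entered as not applicable. Section 3.13.7 has one dose for everyone: "25 mg psilocybin will be administered on day 3".

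**The concern.** There are two separate problems in one paragraph.

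The first is the word blinded. With one arm and one dose there is no allocation to conceal, and the protocol names nothing else that the assessor is kept from knowing. Left in place, the word describes a safeguard that the design does not provide.

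The second is the order of the two steps. The question about the underlying condition works as a gate: an AE that it can explain is never rated against psilocybin. In a PTSD population many plausible drug effects resemble the illness. Section 2.1 lists irritability, poor sleep, poor concentration and changes in mood among PTSD symptoms, and section 3.10.2 links dissociation to PTSD. Section 4.1.8 lists dissociative disorder, altered mood and disturbed attention as events of special interest for the study drug. These are the events for which a causality rating is most informative, and the gate may leave them without one.

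At stake is whatever the protocol makes depend on relatedness:
- the section 2.6.4 aim of determining how treatment-emergent AEs relate to psilocybin;
- the documentation of AEs found after the last visit (4.1.9);
- the reporting of late serious events assessed as related (4.1.10);
- the expedited reporting of serious unexpected adverse drug reactions (4.1.11).

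**Working it through.** The plan gives no figure to reproduce here. The check is a comparison of texts, followed by an illustration of scale.

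**1. Blinding against design.** Section 4.1.2 needs a blinded assessor. The Study Summary gives open-label, single arm, masking not applicable, and section 3.13.7 gives every participant the same dose. The independent rater in section 7.1 is for outcome measures and is not assigned AE causality. No passage gives the word a meaning. It may be carried over from a controlled trial: section 4.6 likewise refers to a randomisation number, which this trial cannot have.

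**2. Section 4.1.2 against 4.1.6.**

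| | 4.1.2 | 4.1.6 |
|---|---|---|
| Which AEs are rated against psilocybin | Only those the underlying condition does not explain | Each AE |
| Assessor | A blinded study investigator first, then the study investigator | The investigator |
| Preliminary gate | Yes | None |

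For an AE that the underlying condition can explain, 4.1.2 yields no psilocybin category and 4.1.6 asks for a causal assessment.

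**3. Section 4.1.2 against its own scale.** *Unlikely* includes events that the clinical state may have produced. *Possible* admits events that other factors could readily have caused. *Probable* already asks whether the clinical state could reasonably account for the event. The scale therefore weighs the underlying condition within the rating, while the gate removes such events before the scale is applied.

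**4. Direction.** The gate can take events out of the psilocybin-related categories but cannot add any. Any effect on a count of related AEs is downward or nil.

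**5. Illustration of scale.** Section 2.4 gives transient anxiety at psilocybin onset as 20-100%, and section 3.2.1 gives n = 15.
- Expected participants with it: 15 × 0.20 = 3 to 15 × 1.00 = 15.
- Chance of at least one at the 20% rate, treating participants as independent: 1 − 0.8^15 = 0.965.
- Let f be the share judged explainable by the underlying condition. The expected number of participants whose onset anxiety goes unrated is 15 × p × f. With f = 0 this is 0. With f = 1 it is 3 when p = 0.20 and 15 when p = 1.00.

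The documents give no value for f, so the range stays at none to all. The number entering causality review may also be below 15 × p, because section 2.4 lets investigators not treat expected intrapsychic reports as AEs.

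**6. What does not change.** Section 3.10.1 sets the tolerability threshold on the percentage of participants with AEs (at most 20%), with no restriction to related events. Section 7.1 tabulates AEs and serious AEs by type and does not mention relatedness.

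**The case against.** The best defence is that the two sections can be read together: 4.1.6 names the field and 4.1.2 says how it is filled, so a decision that the underlying condition explains an AE is itself a causal judgement. This has some force, since a site could work that way. But 4.1.2 does not say which category such an event receives, and its own *Unlikely* and *Possible* definitions imply that the event should have reached the scale. The texts still need reconciling.

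Second, the events do not disappear. Section 4.1 counts worsening of a pre-existing condition as an AE, 4.1.6 records AEs regardless of relatedness, 4.1.8 requires immediate notification of events of special interest with no relatedness condition, and suicidality is followed by C-SSRS through week 13. All of this stands. What may be lost is the rating, not the record.

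Third, the text says underlying condition and does not name PTSD. PTSD is the natural reading, but it is a reading. Onset anxiety during a supervised session is also a weak example, since its timing points to the drug. Both points limit the illustration and leave the contradiction as it is.

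Two stronger inferences are tempting. A reader might conclude that the primary tolerability result is biased. The documents do not support this, because that metric and the AE tables count AEs without regard to relatedness. A reader might also assume a share, such as half, to put a number on the lost ratings. Nothing in the protocol supports any particular share.

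**Conclusion.** The point holds as an inconsistency in the rule for AE causality. The blinding has no stated meaning in this design. The gate conflicts with section 4.1.6 and with the categories that follow it in 4.1.2. The direction of any effect is certain from the text: fewer events rated as related to psilocybin, or no change. The size cannot be computed and lies between none and all of the AEs that overlap with the underlying condition.

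The consequence is confined to the section 2.6.4 objective on the relationship of treatment-emergent AEs to psilocybin and to the identification of related events and adverse drug reactions for reporting (4.1.10 and 4.1.11). It does not reach the primary feasibility and tolerability thresholds. The conclusion assumes that 4.1.2 is followed as written and, for the examples only, that the underlying condition means PTSD. This is a recording rule fixed in the protocol, so it should be corrected before ratings begin.

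**What to change.** - In section 4.1.2, delete the word blinded, or state exactly what the assessor is blinded to and how that is achieved when every participant receives psilocybin.
- Reconcile 4.1.2 with 4.1.6 so that every AE receives a psilocybin causality category. The underlying condition should be weighed within that rating, as the existing category definitions already provide, and not used as a gate before it.

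The cost is a short text change in 4.1.2. No treatment, visit or primary analysis changes. The count of AEs rated as related may be higher than under the present wording.

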###### **2.6.4. Safety**

The safety objectives of the study are to monitor and assure the safety of participants before, during and after the psilocybin dosing session and during the study period by assessing severity, incidence and frequency of physiological effects, psychological distress, spontaneously reported reactions, AEs, Treatment Emergent AEs (TEAEs), AEs of Special Interest (AESIs), serious AEs (SAEs), medical events, concomitant medication use, and suicidal ideation and behavior.

- Suicidality will be assessed using the Columbia Suicide Severity Rating Scale (C-SSRS) according to the schedule of assessment table.
- Before and after the experimental session vital signs including blood pressure, heart rate, and temperature will be collected.
- Medical events requiring a doctor’s visit, medications for treatment and psychiatric medications will be collected.
- Assess incidence of AEs by severity.
- Assess incidence of TEAEs by severity to analytically determine relationship to the psilocybin.
- Assess incidence of AESIs, defined as AEs specified in the protocol related to cardiac function, suicide risk, and abuse liability.
- Assess incidence of AEs.
- Assess incidence of SAEs.

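### Adverse-event causality is rated to psilocybin alone, so harm from the study's own CPT cannot be recorded as related to the combined intervention under test

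*Protocol*

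**What the plan says.** The safety outcome in the Study Summary is "To evaluate the safety of psilocybin-assisted CPT in adults with chronic PTSD". Section 3.6 describes that treatment as 12 CPT sessions, a preparatory and an integration session, and one dosing session within 7 days.

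Section 4.1.2 first asks whether the event can be explained by the underlying condition. If not, "the study investigator will make a determination of the relationship of the AE with psilocybin as follows". The AE record in 4.1.6 likewise holds the investigator's "assessment of the causal relationship between the event and the investigational product". Section 2.6.4 adds the aim "Assess incidence of TEAEs by severity to analytically determine relationship to the psilocybin".

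Three parts of the scale in 4.1.2 matter here:
- *Possible* needs a reasonable time course after the dose and admits an event "but that could readily have been produced by a number of other factors".
- *Unlikely* opens with "Reports not following a reasonable temporal sequence from psilocybin administration".
- *Unlikely* then adds events that may come from the participant's "clinical state or by environmental factors or other therapies administered".

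After the reporting period, 4.1.10 has serious events reported if judged related to psilocybin. Section 4.1.9 instead uses the wider term *study treatment* for AEs found after the last visit.

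**The concern.** The treatment under test is the combination, but the only causal question on the form concerns one component. Trauma-focused therapy, massed into a week, can itself cause distress. Under the scale as written, an investigator who correctly attributes such an event to CPT has nowhere to record that the study intervention caused it, and the scale points to *Unlikely* or *Not related*.

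Benefit and harm are also handled differently. Section 7.1 credits symptom change to psilocybin-assisted CPT as a whole, while harm is attributed to the drug only. The qualitative survey in 3.13.9 does ask participants how psilocybin and CPT each contributed to changes. The AE form does not ask the investigator anything comparable.

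At stake is whether the trial can say which AEs were judged related to the intervention that a larger trial would use. Attribution is a clinical judgement made when the event is recorded. If the form never asks for it, a statistical analysis plan cannot recover it.

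**Working it through.** The plan gives no figure to reproduce, and the point rests on no rate or sample size. The check sets the causality text beside every other place that uses relatedness, then sorts events by cause.

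**1. What relatedness refers to**
- 4.1.2: psilocybin ("make a determination of the relationship of the AE with psilocybin as follows").
- 4.1.6: the investigational product.
- 2.6.4: psilocybin.
- 4.1.10, late serious events: psilocybin.
- 4.1.9, late AEs: study treatment.
- Study Summary, safety outcome: psilocybin-assisted CPT.

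No field records a link to CPT, to the preparatory or integration session, or to the whole intervention. Sections 4.1.9 and 4.1.10 do not use the same reference.

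**2. What happens before the dose**

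Sections 3.10.4 and 4.1.6 start AE collection on day 1. Section 3.6 places CPT sessions 1–4 and the preparatory session on days 1 and 2, and the dose on day 3. So 4 + 1 = 5 of the 12 + 2 = 14 psychotherapy sessions precede dosing, and 8 + 1 = 9 follow it (CPT 5–12 and integration). These counts describe exposure, not how many events are affected.

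**3. Sorting events by cause under 4.1.2**
- *Caused by CPT before the dose.* No time course after psilocybin exists, so the event is *Unlikely* or *Not related*. As a rating for the drug this is right. As a statement about the intervention it is wrong, and nothing else on the form corrects it.
- *Caused by CPT alone after the dose.* If correctly attributed, the event is again *Unlikely* or *Not related*, with no record of the link to CPT.
- *Joint psilocybin and CPT causes, after the dose, with a plausible time course.* The event fits *Possible*, because other factors could have produced it. It also fits the second sentence of *Unlikely*, because another therapy may have produced it. The text does not say whether the two sentences of *Unlikely* must both hold or whether either is enough, so the rating depends on the rater.
- *Worsening judged to be explained by PTSD.* The event stops at the first question and receives no relatedness rating, even if a therapy session set it off.

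**4. Which outputs depend on the rating**
- 4.1.6 records every AE, related or not.
- 3.10.1 defines tolerability as the percentage of participants with AEs, without a relatedness filter.
- 7.1 tabulates AEs and serious AEs by type for the whole sample.

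None of these changes with the causality rating. What does depend on it is the relationship aim in 2.6.4, late SAE reporting in 4.1.10, and any summary of related events made from the form.

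**5. The wording in 2.6.4**

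Incidence by severity is a count. In a single-arm trial where every participant is planned to receive both components, such a count cannot separate psilocybin from CPT or from the course of the disorder. Only the investigator's case-by-case judgement bears on relatedness.

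**The case against.** The strongest reply is that recorded harm does not change. Every AE is collected from day 1, the primary percentage counts any AE, and the planned tables do not use relatedness. The likeliest therapy harms are also measured directly: suicidality by the C-SSRS at every visit, and PTSD symptoms by the PCL-5 on each treatment day. The protocol specifies no count of treatment-related AEs, so no planned figure is biased. All of this stands, and it limits the point to attribution.

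A reader might infer that harm from the combination is automatically excluded from related events. The documents do not support that. *Possible* accepts competing explanations, and *Probable* rules out only explanation by the participant's clinical state. For joint causes the fault is overlapping definitions. A reader might also try to size the problem from the share of sessions that are psychotherapy, but a session count does not measure misclassified events, and the protocol gives no figure that would.

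A drug-specific rating is also legitimate. Section 4.1.11 requires expedited reporting of serious unexpected adverse drug reactions, and a pre-dose event is properly unrelated to the drug. This is a reason to keep that rating, but not to have it alone.

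Finally, if a single-arm trial cannot separate the components, asking investigators to do so may look inconsistent. That tells against relying on finely divided component ratings. It does not tell against one rating for the whole intervention, which needs no such separation.

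**Conclusion.** The point holds as a question of attribution. The safety objective concerns psilocybin-assisted CPT, but no field can record an event as related to that intervention when CPT alone caused it, and joint-cause events after dosing can be rated either way. Total AE and SAE counts and the primary AE percentage are unaffected.

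The number of events concerned cannot be derived from the protocol. The conclusion rests on reading the other-therapies wording as covering study CPT, which the text neither states nor excludes. Even if CPT were excluded from it, the form would still have no place to record relatedness to CPT or to the whole intervention. This is a cheap improvement worth making before AE data are collected, not a flaw that undermines the trial.

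**What to change.** - **4.1.2 and 4.1.6:** keep the psilocybin rating for drug-reaction reporting. Add a rating of relatedness to the study intervention as a whole (psilocybin, CPT, preparatory or integration session), asked for every AE, including those explained by the underlying condition. Add a mark for study psychotherapy as a suspected contributor where the investigator judges so. Summarise AEs by the new rating.
- **4.1.2, *Unlikely*:** state that the other therapies meant are non-study therapies, say whether its two sentences are joint or alternative criteria, and word *Possible* and *Unlikely* so that one event cannot meet both.
- **4.1.9 and 4.1.10:** reconcile the two references, study treatment in one and psilocybin in the other.
- **2.6.4:** replace the claim that incidence by severity determines the relationship analytically with a summary by investigator-rated relatedness.

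The cost is one or two extra fields on the AE form, the wording changes, and possibly a less favourable related-AE figure. No change to the sample size, the visit schedule or the primary outcome is needed.
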